## Abstract

**Background:**

One of the most important aspects of designing a clinical trial is selecting appropriate outcomes. Patient-reported outcomes (PROs) can provide a personal assessment of the burden and impact of a malignant disease and its treatment. PROs comprise a wide range of outcomes including basic clinical symptom scores and complex metrics such as health-related quality of life (HRQoL). There is limited data on how postoperative complications following cancer surgery affect symptoms and HRQoL. For this reason the primary aim of the PATRONUS study is to investigate how perioperative complications affect cancer-related symptoms and HRQoL in patients undergoing abdominal cancer surgery. The PATRONUS study is designed and will be initiated and conducted by medical students under the direct supervision of clinician scientists based on the concept of inquiry-based learning.

**Methods:**

PATRONUS is a non-interventional prospective multicentre cohort study. Patients undergoing elective oncological abdominal surgery will be recruited at regional centres of the clinical network of the German Surgical Society (CHIR-*Net*) and associated hospitals.

A core set of 12 cancer associated symptoms will be assessed via the PRO version of the Common Terminology Criteria for Adverse Events. The cancer-specific HRQoL will be measured via the computerised adaptive testing version of the European Organisation for Research and Treatment of Cancer (EORTC) QLQ-C30. PROs will be measured eight times over a period of six months. The short-term clinical outcome measure is the rate of postoperative complications (grade II to V) within 30 days according to the Clavien-Dindo classification. The long-term clinical outcome is overall survival within six months postoperative.

**Discussion:**

PATRONUS will provide essential insights into the patients’ assessment of their well-being and quality of life in direct relation to clinical outcome parameters following abdominal cancer surgery. Furthermore, PATRONUS will investigate the feasibility of multicentre student-led clinical research.

**Trial registration:**

German Clinical Trials Register: DRKS00013035 (registered on October 26, 2017).

Universal Trial Number (UTN): U1111–1202-8863.

**Electronic supplementary material:**

The online version of this article (10.1186/s12893-018-0422-3) contains supplementary material, which is available to authorized users.

## Background

Cancer is the second most common cause of death in Germany following cardiovascular diseases [1]. Due to demographic changes, the incidence and prevalence of malignancies in Germany will rise sharply within the next years [2–4]. According to German national data, the most frequent lethal tumour diseases include solid neoplasms of the abdominal cavity including pancreatic, liver, gastric and colorectal cancers [5]. For these tumours, surgery is the mainstay of curative as well as palliative treatment. At the same time, cancer patients will become older and comorbid [2, 6, 7]. Therefore patients, caregivers and specialists will face new challenges in the care of cancer patients. Accordingly the design and focus of clinical trials will need to adapt to this changing environment with an increasing need to integrate the patients’ perspective in clinical studies.

For this purpose, patient-reported outcomes (PROs) have been introduced next to survival and morbidity endpoints in oncological trials. PROs can be defined as ‘any outcome evaluated directly by the patient himself or herself and is based on the patient’s perception of a disease and its treatment(s)’ [8] and are measured via validated PRO measures (PROMs). PROMs in oncological trials can be classified into two main groups: PROMs for the assessment of cancer- and treatment-related symptoms and PROMs to measure health-related quality of life (HRQoL) [9]. Recently, two new PROMs have been proposed for each purpose: the EORTC has evaluated a digital, computer adaptive testing (CAT) version of their widely used cancer-specific HRQoL questionnaire C30 (CAT EORTC QLQ-C30) [10–12] and the National Cancer Institute (NCI) has validated a PROM version of the Common Terminology Criteria for Adverse Events (PRO-CTCAE) to measure cancer or treatment associated symptoms [13]. In addition, the NCI has defined a core-set of 12 symptoms that should be reported in all cancer trials [14].

PROs can provide additional benefit in clinical trials as they might provide a personal assessment of the burden of a malignant disease and its treatment and might complement survival, morbidity and safety data, thus enabling a full risk-benefit assessment [8]. Although PROs have been applied frequently in cancer trials, astonishingly little is known about the relationship between clinical endpoints and the well-being of cancer patients undergoing abdominal surgery. Arguably the most important clinical outcome in surgical oncology from a patient’s point of view is, apart from survival, the frequency and severity of complications. To this end the Clavien-Dindo classification which grades postoperative complications according to their sequelae has gained wide acceptance [15, 16]. Although it seems intuitive that complications adversely affect HRQoL and symptoms, the extent to which HRQoL and symptoms are affected is unknown. It is therefore also unclear whether complications considered more severe in the Clavien-Dindo classification system [15, 16], i.e. those with a higher severity grade, are related to reduced HRQoL or symptoms. Although several cross-sectional studies have evaluated HRQoL in patients who had undergone oncological abdominal surgery and found an association between postoperative complications and decreased long-term HRQoL [17–19], these results are questionable considering the design of these studies and their insufficient validity [20]. Most of the few available prospective trials have been performed exclusively in colorectal cancer surgery and show heterogeneous results, with some demonstrating no [21], some short-term [22] and some also long-term effects of complications on certain subdomains of HRQoL [23, 24]. For other cancers of the gastrointestinal tract, including pancreatic [25] and oesophageal cancer [26], data are even more sparse. Furthermore, the majority of these studies exhibit severe methodological limitations including single-centre design, limited number of patients, inadequate follow-up, and high rate of missing data. Finally, all of these studies used a wide range of different PROMs and frequently no standardised morbidity assessment. Therefore, a prospective multicentre study using validated complication measurements and PROMs seems urgently warranted.

### Student-led clinical research and learning-by-research

Although the principles of evidence-based medicine (EbM) are taught in most medical schools, the focus of most EbM curricula is on the application of EbM-principles in everyday clinical practice, but not on teaching scientific methodology or performing scientific work, i.e. generating new scientific evidence. Consequently, a future deficit in academic faculty seems likely in European countries [27–29].

Inquiry-based learning or learning-by-research are concepts that refer to a trend in higher education: to provide students with the opportunity to gain knowledge by conducting their own scientific inquiries or investigations. Although the underlying mechanisms still have to be revealed, projects to provide such research experiences are emerging and show that medical students can improve their clinical capabilities by contributing to student-initiated clinical trials [30–32]. Recently, a student-led initiative has successfully performed a number of large observational studies in a national cohort following gastrointestinal surgery demonstrating the feasibility of this concept [33, 34]. On an even larger scale the EuroSurg collaborative demonstrated the feasibility of this concept across 20 European countries [35]. However, all of these studies were confined to specific subpopulations of patients, excluded PROMs and investigated specific rather than all postoperative complications. The study idea for the PATRONUS study was conceived by the Study network of the German Surgical Society (CHIR-*Net*; www.chir-net.de). CHIR-*Net* has succeeded in creating a German-wide research infrastructure comprising university and non-university centres. Since its foundation in 2006, CHIR-*Net* has recruited more than 11,800 patients in randomised-controlled surgical trials and consists of 16 regional centres and their associated partner hospitals [36]. CHIR-*Net* has recently created a student-led clinical trial network (Student-initiated German Medical Audit, SIGMA; www.sigma.university) [37] which will run the PATRONUS study.

## Methods/design

This study protocol is written according to current SPIRIT guidelines [38]. The SPIRIT checklist is attached as Additional file 1.

### Study design

PATRONUS is a prospective multicentre single-arm observational cohort study across Germany.

### Outcome measures

#### Patient-reported outcome measures (PROMs)

a core set of 12 cancer associated symptoms [14] (fatigue, insomnia, pain, anorexia, dyspnoea, cognitive problems, anxiety, nausea, depression, neuropathy, constipation, diarrhoea) measured via the PRO-CTCAE [13].cancer-specific HRQoL measured via the CAT EORTC QLQ-C30 [39, 40].

#### Clinical outcome measures

Short-term clinical outcome measure is the rate of postoperative complications grade II (minor) and III-V (major) within 30 days according to the Clavien-Dindo classification [15].Long-term clinical outcome is overall survival within 6 months postoperative.

### Objectives

The primary aim of the study is to evaluate associations between the clinical outcomes and the two PROMs in the short-term (within 30 days) and long-term (after 3 and 6 months) in order to find out whether and to what extend complications (none/grade I vs. minor (grade II) vs. major (grade III-V)) influence the two PROMS in 5 predefined surgical cancer subgroups (upper-GI, pancreatic, hepatobiliary, colorectal, other abdominal cancers).

Further objectives are:To describe the absolute values of a.) the newly defined CAT EORTC QLQ-C30 and b.) the set of 12 cancer-specific symptoms [14] measured via the PRO-CTCAE [13] for oncologic patients undergoing surgery at predefined times from baseline (preoperative) until 6 months postoperative in the 5 surgical cancer subgroups outlined above.Although both of the proposed PROMs (PRO-CTCAE [13] and CAT version of the EORTC QLQ-C30) used in this trial have been validated, they are new and have never been tested head-to-head. Therefore, the existence of possible overlapping domains in both PROMs will be analysed.In order to find out if a student-led multicentre observational study using an electronic data capture system is feasible.

For the primary objective and further objective 1. and 2., the two PROMs (PRO-CTCAE and CAT version of the EORTC QLQ-C30) in the short-term (within 30 days) and long-term (after 3 and 6 months), as well as is the rate of postoperative complications grade II (minor) and III-V (major) within 30 days according to the Clavien-Dindo classification and the overall survival within 6 months postoperative will be assessed.

For further objective 3 the following endpoints will be assessed:Rate of missing PRO data at 3 and 6 monthsRate of missing clinical data at 30 daysNumber of participating trial sites including patients compared to initiated trial sitesRate of included patients in comparison to screened patients

Further endpoints can be found in the description of the study visits.

### Study duration and schedule

The duration of the study for each patient is 6 months including follow-up. Milestones are listed in Table 1. The duration of the overall study is expected to be 18 months. Figure 1 displays the patient flow during the study.

**Table 1 Tab1:** Milestones and study time plan

1	Preparation of trial, Ethic votes, database set-up	3 months
2	Initiation, training course for participants (including preparation) (overlap with 1)	1 month
3	Recruitment period	2 months
5	Follow-up period	6 months per patient
7	query management, database clearing	3 months
8	Report, publication	3 months
Total		18 months

**Fig. 1 Fig1:**
[figure not shown]
Patient flow chart. *CAT* computer adaptive testing version, *CTCAE* Common Terminology Criteria of Adverse Events, *EORTC* European Organisation for Research and Treatment of Cancer, *HRQoL* health-related quality of life, *PRO* patient-reported outcome, *PROM* patient reported outcome measure

### Study conduct and study centres

To enrol an adequate number of patients in the planned recruitment period, 30 hospitals including regional centres of the clinical trial network CHIR-*Net* (www.chir-net.de/regionalzentren-karte) as well as associated partner-hospitals will participate in the study.

A CHIR-*Net* SIGMA steering group for the PATRONUS study has been set up consisting of the authors of this publication and include the CHIR-*Net* coordination centre. This steering group has designed the study and is responsible for trial infrastructure, acquisition of centres, qualification of participating medical students and communication with centres and the public via digital tools (www.slack.com) and social media (www.facebook.com/sigmastudynetwork; https://twitter.com/sigmastudies).

At each trial site a so-called “mini-team” will be established consisting of an experienced clinical trialist (surgeon) and a group of at least two medical students. Furthermore, at each site a “local lead” will be appointed. The local lead is a medical student responsible for creating the mini-team, recruiting other students to the project, interacting with local surgeons and conducting the study. The local lead in conjunction with the associated surgeon is also responsible for gaining approval for the study from his/her local independent ethics committee according to the German Medical Association’s professional code (*Berufsordnung der Bundesärztekammer*).

All student participants will be trained prior to study initiation. To this end CHIR-*Net* SIGMA has developed an in-person and online clinical trials training programme (SIGMA clinical trial curriculum; SIGMA-CTC) which will be reported elsewhere.

### Interventions

No experimental or control intervention is tested as this is an observational, non-interventional prospective cohort study.

### Eligibility criteria

Every local team will recruit patients for the study independently. Inclusion criteria are: a.) patient’s age ≥ 18 years; b.) patient scheduled for elective abdominal surgery for confirmed or suspected malignancy; c.) patient’s ability to understand character of the study; d.) planned laparoscopic or open surgery or any variant (i.e. laparoscopic-assisted, laparoscopic-thoracoscopic), e.) written informed consent. Exclusion criteria are a.) language barrier that impedes follow-up or informed consent, b.) American Society of Anesthesiologists (ASA) grade ≥ 4.

All patients planned for an elective surgery for suspected or confirmed malignancy are asked for their participation in the trial if all inclusion criteria and none of the exclusion criteria are fulfilled. Screening lists are kept in order to analyse reasons for non-inclusion of patients and to calculate the case ascertainment rate.

### Patient timelines and description of study visits

Patients will be screened preoperatively (visit 1) by a member of the mini-team. Patients will be enrolled if they fulfil the inclusion/exclusion criteria and after having given their written informed consent after detailed patient information. Informed consent is sought by a member of the mini-team, i.e. medical student or clinical trialist (surgeon). Baseline data and the first set of PROMs are collected during screening/baseline visit. Surgical data is collected during visit 2. Short-term clinical outcome parameters and PROMs are collected during visits 3–6 within 30 postoperative days or until discharge. Long-term clinical data and PROMs are collected at visit 7 and 8. Detailed information about the collected data during the patients’ visits is displayed in Table 2 (SPIRIT figure).

**Table 2 Tab2:** Adapted SPIRIT figure showing the visits and documented parameters of the PATRONUS study

Activity	Visit 1 (screening, consent)	Visit 2 (surgery)	Visit 3–6 (POD 3–5, 6–8, 10–14, 30–35 or at discharge)	Visit 6_TEL_ (POD 30–35 if patient has been discharged before)	Visit 7/8 (postoperative month 3 and 6)
expenditure of time per visit approx	20–25 min	–	15 min	15 min	15 min
Inclusion/exclusion criteria	X				
Informed consent	X				
Demographics and baseline data	X				
Documentation of PROMs: a.) 12 symptoms PRO-CTCAE* b.) cancer-specific HRQoL**	X		X^§^	X	X
Surgery		X			
Postoperative morbidity***			X	X	
SSI^$^			X	X	
Length of hospital stay			X	X	X
Reoperations			X	X	X
(Re)admissions			X	X	X
Overall survival			X	X	X

* 12 symptoms as recommended by the National Cancer Institute: fatigue, insomnia, pain, anorexia, dyspnoea, cognitive problems, anxiety, nausea, depression, neuropathy, constipation, diarrhoea assessed via PRO-CTCAE™

** according to the EORTC quality of life questionnaire C30

*** according to Clavien-Dindo

^$^ Documentation of SSI according to CDC [40, 41]

^§^ HRQoL once only on POD 30–35 or at discharge (Visit 6)

TEL Visit can be performed by telephone

*SSI* surgical site infection, *CDC* Centers of Disease Control and Prevention, *POD* postoperative day, *OS* overall survival, *PROM* patient-reported outcome measure, *CTCAE* Common Terminology Criteria of Adverse Events, *HRQoL* health-related quality of life

#### Visit 1 (preoperative, informed consent)

After informed consent, the following data items will be collected during visit 1: a.) demographic data; c.) baseline data d.) previous abdominal surgeries; e.) medical history; f.) HRQoL according to CAT EORTC QLQ-C30 [39, 40]; g.) PRO-CTCAE [13] of 12 core cancer-associated symptoms [14].

#### Visit 2 (surgery)

During surgery, the following parameters will be recorded: a.) duration of surgery; b.) estimated blood loss; c.) intraoperative blood transfusion; d.) surgery performed including completeness of macroscopic tumour resection; e.) category of surgery (upper-GI, pancreatic, hepatobiliary, colorectal, other); f.) degree of contamination according to the Centers for Disease Control and Prevention (CDC) definition [41].

#### Visit 3 (postoperative day 3–5)

This visit is performed to document short-term clinical outcome (complication rate). The following data items need to be documented: a.) survival; b.) discharge; c.) PRO-CTCAE symptoms; d.) reoperation(s); e.) complications according to Clavien-Dindo; f.) surgical site infections (SSI) including grading according to the CDC classification [41]; g.) weight.

#### Visit 4 (postoperative day 6–8)

Visit 4 has an equivalent content to visit 3, with the exception of the PRO-CTCAE symptoms, which are NOT documented during visit 4. If the patient is discharged before day 6–8, visit 4 is omitted.

#### Visit 5 (postoperative day 10–14)

Visit 5 has an equivalent content to visit 3. If the patient is discharged before day 10, visit 5 is omitted.

#### Visit 6 (postoperative day 30–35 or at discharge)

Visit 6 is performed once between postoperative day 30–35 or at discharge if the patient leaves before day 30. The following data items need to be documented: a.) survival; b.) PRO-CTCAE symptoms; c.) CAT EORTC QLQ-C30; d.) reoperation(s); e.) complication assessment according to the Clavien-Dindo classification; f.) SSI assessment according to the CDC classification; g.) weight.

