#### Visit 6_TEL_ (postoperative day 30–35)

Visit 6_TEL_ is performed if the patient has been discharged before postoperative day 30–35. If the patient is still in hospital on day 30–35 visit 6_TEL_ is omitted. The visit should be conducted between day 30–35. This visit can be performed in person (outpatient clinic) or, if the patient cannot be seen in person, on the phone. The following data items have to be collected: a.) survival; b.) PRO-CTCAE symptoms; c.) CAT EORTC QLQ-C30; d.) reoperation(s); e.) (re-)hospitalization; f.) complication assessment according to the Clavien-Dindo classification; g.) SSI assessment according to the CDC classification; h.) details of postoperative oncological treatment; i.) weight.

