#### Event Visit_1-x_ (anytime between visit 1–8)

Event visits are optional, i.e. they do not have to be performed but can be performed if necessary. The objective is to document survival, complications and/or PROs anytime during the study, i.e. between visit 1–8, if they are not covered by the other visits. The following data items should be collected: a.) date; b.) PRO-CTCAE; c.) CAT EORTC QLQ-C30; d.) survival; e.) reoperation(s); f.) hospitalization/readmission; g.) SSI assessment according to the CDC classification; h.) complication assessment according to the Clavien-Dindo classification; i.) oncological treatment; j.) weight.

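### The stated short-term window points to discharge-day and inpatient-only PROM values, whose timing can depend on complications; the day 30–35 assessment should be named as the short-term value

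*Protocol article*

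**What the plan says.** Under Objectives, the primary aim relates complications (none or grade I, grade II, grade III–V) to both PROMs, in the short term (the first 30 days) and in the long term (3 and 6 months).

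The section on patient timelines says when the short-term values are obtained: "Short-term clinical outcome parameters and PROMs are collected during visits 3–6 within 30 postoperative days or until discharge". The Table 2 footnote to the visit 3–6 column allows a single HRQoL measurement there, at visit 6, which falls on day 30–35 or at discharge. The visit 6 section confirms this: "Visit 6 is performed once between postoperative day 30–35 or at discharge if the patient leaves before day 30". For visit 5, which includes PRO-CTCAE, "If the patient is discharged before day 10, visit 5 is omitted".

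A further assessment stands in its own section and its own Table 2 column: "Visit 6_TEL_ is performed if the patient has been discharged before postoperative day 30–35". On its timing: "The visit should be conducted between day 30–35". It collects both instruments, in person or by telephone.

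Statistical procedures names Spearman's rho and analysis of variance for the association in the short and long term. It does not say which visit supplies the short-term value, and it mentions no term for postoperative day.

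**The concern.** Length of stay lies between the exposure and the measurement. A patient with an uneventful course may have visit 6 about a week after surgery, while a patient with a major complication may have it several weeks after. Comparing visit 6 values across Clavien-Dindo groups then compares different stages of recovery. At visit 5 the problem is selection: the uncomplicated patients who are measured are those who, for some other reason, were still in hospital at day 10.

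At stake is the short-term half of the primary aim. Extra recovery time in the complicated group can offset a real deficit, so a weak or reversed association could be produced by the visit schedule alone.

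**Working it through.** The plan gives no figure on this point, so there is none to reproduce. The check has two parts.

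**1. Which postoperative PROM values up to day 35 share a common time?** (From the visit sections and Table 2.)

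| Occasion | Day | Who | PRO-CTCAE | QLQ-C30 |
|---|---|---|---|---|
| Visit 3 | 3–5 | no discharge exception stated | yes | no |
| Visit 4 | 6–8 | inpatients | no | no |
| Visit 5 | 10–14 | inpatients only | yes | no |
| Visit 6 at discharge | day of discharge, before day 30 | discharged before day 30 | yes | yes |
| Visit 6 in hospital | 30–35 | still inpatients | yes | yes |
| Visit 6TEL | 30–35 | discharged earlier | yes | yes |

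Visit 4 adds nothing here; its section repeats visit 3 "with the exception of the PRO-CTCAE symptoms, which are NOT documented during visit 4".

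Visit 5 and the discharge-day visit 6 depend on length of stay. Visit 3 does not. Nor does the day 30–35 assessment, which is due from every surviving patient through one of two routes.

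The stated definition fits the wrong rows. The sentence on short-term PROMs lists visits 3–6, while visit 6TEL has a separate column. Days 31–35 also fall outside a literal 30-day window, whereas a discharge before day 30 falls inside it. For a patient who leaves early, the only HRQoL value that meets both conditions is the discharge-day one.

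**2. How far could timing move the contrast?** All inputs below are assumptions; none is in the documents.

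*Linear recovery.* Shift = recovery per day × gap in discharge day.
- Low: 0.02 SD × 8 days = 0.16 SD.
- High: 0.05 SD × 16 days = 0.80 SD.
- A true deficit of 0.5 SD would appear as 0.5 − 0.16 = 0.34 SD worse at one end and 0.80 − 0.5 = 0.30 SD better at the other.

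*Recovery that levels off.* Score(t) = 70 − (30 + c)·exp(−t/τ), in arbitrary points, where c is the extra initial deficit after a major complication. Take τ = 10, 20 or 30 days, with discharge on day 7, 8 or 10 without a complication and on day 12, 20 or 28 respectively with one.
- No true effect (c = 0): the complicated group looks better at discharge by 30·[exp(−7/30) − exp(−12/30)] = 3.6 points at the least and 30·[exp(−10/20) − exp(−28/20)] = 10.8 points at the most.
- True effect (c = 10): the gap on the same day, 10·exp(−t/τ) at the earlier discharge day, is 3.7 to 7.9 points worse. The at-discharge contrast runs from 8.6 points better (τ = 10, days 10 and 28) to 3.1 points worse (τ = 30, days 7 and 12).
- At a common day 32 the timing artefact is 0. The contrast equals the remaining true gap: 0 for c = 0, and 0.4 to 3.4 points for c = 10.

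Both models show that shrinkage or reversal is possible under plausible-looking inputs. Neither estimates its size in this study.

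**The case against.** The strongest reply is that the design already contains the remedy. Visit 6TEL gives both PROMs at day 30–35 for everyone discharged earlier, and visit 3 has a fixed window. The article never says that visit 5 or discharge values will be contrasted between groups. It defers details to an analysis plan that is not shown, and naming the analysis visit is ordinary content for such a plan. Measuring at discharge is also legitimate as description.

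Most of this stands. A reader might infer that PROM collection stops at discharge, or that the short-term comparison is biased as designed. The visit 6TEL section contradicts the first inference. The second holds only if the length-of-stay-dependent values are used, or are pooled with the day 30–35 values.

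A reader might also infer that complication-triggered PROMs from event visits enter the scheduled comparisons. The article says only that "Event visits are optional, i.e. they do not have to be performed but can be performed if necessary", and nothing states that their values are pooled.

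The numerical illustrations are open to challenge too. They start recovery from surgery in both groups. A late complication or reoperation could restart it, so later measurement need not favour the complicated group.

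What does not stand is that this is merely detail left to the analysis plan. The article does state a short-term definition. That definition points to the discharge value and, read literally, leaves out visit 6TEL and days 31–35.

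**Conclusion.** The point holds conditionally. The stated short-term window, taken at its word, selects PROM values whose day of measurement (visit 6 at discharge) or availability (visit 5) depends on length of stay. If those values feed the rank correlations or the analysis of variance, time since surgery and selection are confounded with complication grade, and the association can shrink or change sign. This rests on one assumption from outside the document: that complications prolong the stay. The magnitude is unknown.

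Severity is moderate. The analyses are exploratory and descriptive, no stated power or error rate is affected, the 3- and 6-month contrasts are untouched, and the data needed for a common-time comparison are already scheduled.

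**What to change.** - Name the day 30–35 assessment (visit 6 if still in hospital, otherwise visit 6TEL) as the main short-term value for both instruments.
- Keep visit 3 PRO-CTCAE as an early comparison at a fixed time.
- Align three places with the visit 6TEL section: the 30-day wording under Objectives, the sentence on short-term PROMs under patient timelines, and the HRQoL footnote to Table 2. State the window so that days 31–35 are clearly inside it.
- Report visit 5, discharge and event-visit PROMs descriptively with their postoperative day. Compare them between complication groups only in a longitudinal model that uses the actual postoperative day.

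The cost is wording in the protocol and analysis plan; no visit or questionnaire is added. There are two small downsides: discharge-day PROMs no longer feed the main short-term contrast, and some patients may not respond at visit 6TEL.
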